### Secondary outcomes measures

Participants will complete a batch of standardised questionnaires at follow-up assessments (see below) to be conducted at 4, 8 and 12 weeks post-randomisation (Table 1 shows the full assessment schedule). Participants will be invited to follow-up assessments unless they have completely withdrawn from the feasibility trial. Questionnaires used for the secondary outcome measures will help to:
Assess the feasibility of delivering these measures within an RCT context;Assess rates of missing data as this will inform the use of these outcomes in a full trial;Estimate variance in these outcomes as this will guide the power calculations for the full trial.

**Table 1 Tab1:** Timing of outcome measurement

***List of questionnaire***	***Baseline***	***Follow-up 1***	***Follow-up 2***	***Follow-up 3***
*Demographic information*	*X*			
*ABUSI*	*X*	*X*	*X*	*X*
*AEP Form (A/B)*		*X*		*X*
*Beck Depression Inventory*	*X*	*X*	*X*	*X*
*CORE-10*	*X*	*X*	*X*	*X*
*ERQ*	*X*	*X*	*X*	*X*
*EQ-5D*	*X*			*X*
*HAq-II*	*X*	*X*	*X*	*X*
*SITBI 2.1*	*X*	*X*	*X*	*X*
*CSRI*				*X*

### Self-Injurious Thoughts and Behaviours Interview Short-Form (SITBI)

The SITBI is a brief interview-based measure that uniformly assesses the presence, frequency and characteristics of information on self-harm related thoughts and behaviours. Repeated self-harm during the feasibility trial period will be captured within the interview. The SITBI has demonstrated interrater reliability, test-retest reliability and convergent validity [41].

### Beck Depression Inventory-II (BDI II)

The BDI II is an established self-report measure of depressive symptoms over the past 2 weeks. There is evidence for the reliability and validity of this measure in the general population [36, 42]. Each of the 21 items on the questionnaire has a choice of four answers scored from 0 to 3. A combined score 0–13 is considered minimal depression, 14–19 mild depression, 20–28 moderate depression and 29–63 severe depression. The questionnaire takes approximately 10 min to complete.

### Frequency/Intensity of self-harm urges-Alexian Brothers Urge to Self-Injure Scale (ABUSI)

The ABUSI is a validated tool designed to evaluate the frequency and intensity of urges to self-injure over the past 7 days [43]. The scale has demonstrated good psychometric properties. The scale measures urge, regularity and strength of self-injurious thoughts across five 7-point scales. Higher scores (up to a maximum of 30) indicate a stronger desire to self-harm.

### Emotion Regulation Questionnaire (ERQ)

The ERQ is a widely validated ten item questionnaire that assesses the way in which individuals regulate their emotions, including the use of re-appraisal and suppression of emotions [44]. The scale has demonstrated good psychometric properties. Higher scores (up to a maximum of 70) indicate greater use of a particular regulation strategy.

### Clinical Outcomes in Routine Evaluation (CORE-10)

The CORE-10 is widely validated, brief ten-item measure of psychological distress over the past 7 days [45]. Higher scores signpost higher levels of psychological distress. A combined score of less than 10 falls in the non-clinical range, 11 to 14 indicates mild psychological distress, 15 to 19 moderate psychological distress, 20 to 24 moderate psychological distress and 25 or above indicates severe psychological distress.

### The Helping Relationship Questionnaire (HRQ)

The HRQ is an 11-item questionnaire that measures patient’s perception of the therapist-patient relationship [46]. The questionnaire is validated and has established psychometric properties. The questionnaire uses a six-point scale, with higher total scores indicating greater therapeutic alliance

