### Design

The study is a single-blind, randomised controlled feasibility trial with an embedded qualitative process evaluation. Participants will be randomised 1:1 to receive COPESS plus treatment-as-usual (TAU) or TAU alone.

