### Randomisation and blinding

Following the collection of baseline data, eligible and consenting participants will be randomly allocated (1:1) by the study statistician, to receive COPESS plus TAU or TAU alone. An algorithm within STATA 15 will be used to generate random allocation sequences in blocks of size of 4 or 6. Block sizes will occur with equal frequency and will be determined at random. The statistician generating the randomisation schedule will be independent from other elements of the project to maintain allocation concealment. Blinding is an important methodologic feature of an RCT that aims to reduce bias [34]; however, in psychotherapy trials, complete blinding is not possible as the participants cannot be blind to whether they receive therapy or not. Participants will be reminded to keep the researcher blind to their allocation arm of the study. Once randomisation has taken place the statistician will inform the study PI of patient arm allocation. The PI will inform both the patient and their GP, keeping the researcher completing study assessments masked to treatment allocation. This will be facilitated by briefing members of the research team and participants on the need to avoid disclosure of treatment details (see Fig. 2). A record will be kept of how many times accidental unblinding occurs. See Fig. 3 for full timeline of events.

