### Primary outcome

The primary outcome of this feasibility study is the feasibility and acceptability of using COPESS for people in the community who self-harm and have co-existing depression. Feasibility will be defined as the ability to recruit the target sample size and retain at least 70% of participants in both arms of the trial over the 3 -month follow-up period. Acceptability of the intervention will be assessed by the percentage of participants who engage and are retained in therapy (acceptability requires > 40% randomised to COPESS to attend all sessions) with contextual data collected from semi-structured qualitative interviews focusing on participants’ experience of the therapy. Acceptability of the intervention for therapists will also be assessed by semi-structured qualitative interview. Acceptability of the trial measures will be defined as the proportion of participants who complete each of the measures at all assessment points (acceptability requires at least 80% of questionnaires completed), supplemented by semi-structured interview data.

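### The alliance measure has two names, is scheduled at baseline before any trial therapist exists, and is counted in the 80% completion criterion without stating to whom it applies

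*Protocol article*

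**What the plan says.** Three parts of the protocol article bear on this.

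- **Instrument.** The section on the Helping Relationship Questionnaire states: "The HRQ is an 11-item questionnaire that measures" the patient's view of the relationship with the therapist, with "higher total scores indicating greater therapeutic alliance". Table 1 (Secondary outcomes measures) has no HRQ row. It has a row for HAq-II, a name that appears nowhere else.
- **Schedule.** Table 1 marks HAq-II at baseline and at follow-ups 1, 2 and 3. The text above it says "Participants will complete a batch of standardised questionnaires at follow-up assessments", "to be conducted at 4, 8 and 12 weeks post-randomisation", without distinguishing arms. Under Randomisation and blinding, allocation comes after baseline data are collected. Under Design, "Participants will be randomised 1:1 to receive COPESS plus treatment-as-usual (TAU) or TAU alone".
- **Criterion.** Under Primary outcome, acceptability of the trial measures is the share of participants who "complete each of the measures at all assessment points". The threshold is then given as 80% of questionnaires completed.

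**The concern.** One purpose of the trial is to test the measures for a definitive trial. If the text and the schedule name different alliance measures, the results cannot be attributed to either until the names are reconciled.

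The schedule adds a second difficulty. An alliance form needs a therapist to rate. At baseline no participant in either arm has a trial therapist, and the TAU-alone arm does not receive one later. The form nevertheless enters a primary acceptability criterion that counts every measure at every assessment point. A low completion figure could then reflect forms that did not apply, when the criterion is meant to show whether participants found the measures acceptable.

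**Working it through.** The plan gives no completion figure to reproduce. Its one precision statement (Sample size: attrition of 35% to within 12 points, N = 60) checks out, since 1.96 × √(0.35 × 0.65 / 60) = 12.1 points, but nothing below depends on it.

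**Inputs.** N = 60 (Sample size), allocated 1:1, so 30 per arm. Visits and forms come from Table 1. The threshold of 80% and the retention criterion of 70% come from Primary outcome. I take the HAq-II row to be the alliance measure: it is the only questionnaire row with no description in the text, and HRQ is the only described instrument with no row.

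**Working assumptions.** An inapplicable form counts as not completed, and only a trial therapist can be rated. The second assumption is varied below.

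**Per-measure reading**

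- Baseline: 0/60 = 0%.
- Each follow-up: at most 30/60 = 50%. This is generous at week 4 if some COPESS participants have not yet started therapy.
- All scheduled alliance forms: (3 × 30)/(4 × 60) = 90/240 = 37.5%.
- Participants with a valid form at all four points: 0%.
- If a share *f* of TAU participants rate another therapist, the follow-up ceiling is (30 + 30*f*)/60. It runs from 50% (*f* = 0) to 100% (*f* = 1) and reaches 80% at *f* = 0.6.
- With *f* = 1 but no therapist at baseline, the four-visit ceiling is 180/240 = 75%, still below 80%.

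**Pooled reading**

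Leaving out demographics, Table 1 gives 4 (ABUSI) + 2 (AEP) + 4 (BDI) + 4 (CORE-10) + 4 (ERQ) + 2 (EQ-5D) + 4 (HAq-II) + 4 (SITBI) + 1 (CSRI) = 29 forms per participant: 7 at baseline and 22 at follow-up. The total is 60 × 29 = 1740.

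- Inapplicable alliance forms: 60 at baseline + 30 × 3 in TAU = 150.
- Ceiling before attrition: (1740 − 150)/1740 = 1590/1740 = 91.4%.

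Now let a fraction *r* of each arm attend every follow-up and complete all applicable forms, with baseline otherwise complete. Completed forms are 60 × 6 + *r*(30 × 22 + 30 × 19) = 360 + 1230*r*. Without any alliance form they are 360 + 1140*r* out of 60 × 25 = 1500. With the form kept only at COPESS follow-ups, the denominator is 1500 + 90 = 1590.

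| Retention *r* | As scheduled (/1740) | No alliance form (/1500) | COPESS follow-ups only (/1590) |
|---|---|---|---|
| 90% | 1467 = 84.3% | 1386 = 92.4% | 1467 = 92.3% |
| 80% | 1344 = 77.2% | 1272 = 84.8% | 1344 = 84.5% |
| 70% | 1221 = 70.2% | 1158 = 77.2% | 1221 = 76.8% |

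The retention needed for 80% pooled completion is (0.8 × 1740 − 360)/1230 = 83.9% as scheduled, against (0.8 × 1590 − 360)/1230 = 74.1% if only applicable forms count.

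**Sensitivity at 80% retention.** If a share *f* of TAU participants can rate another therapist, completed forms become 1344 + 72*f*. Pooled completion then runs from 77.2% (*f* = 0) to 1416/1740 = 81.4% (*f* = 1) and crosses 80% at *f* = 48/72 = 0.67.

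**The case against.** The strongest reply is that the criterion does not have to fail.

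- **Pooled threshold.** The 80% is worded as a percentage of questionnaires, so it can be read across all forms. A reader might infer that the trial cannot meet its own rule. The documents do not support that, because the pooled ceiling is 91.4%.
- **Inapplicable forms.** Nothing says that they count as not completed. The Statistical analysis section plans to examine types of missing data, which leaves room to separate them. This stands, and it is why the denominator should be stated.
- **Other therapists.** The exclusion covers only current face-to-face talking therapy for self-harm. Group counselling and nurse appointments are allowed, recruitment material is displayed in counselling and therapy services, and TAU is unrestricted. Some participants may therefore have a non-trial therapist, at baseline or later. This also stands. The ceilings of 0% and 50% are for ratings of a trial therapist, and the protocol does not say whether anyone else should be rated.
- **Arm restriction.** Use in TAU is inferred from the absence of a restriction. Table 1 has no arm columns and Fig. 3 is not available here. The baseline entry, however, is printed and does not depend on that inference.
- **The two names.** HAq-II is undescribed, so the documents cannot show whether it is a second instrument or a labelling slip. Either way the two places need reconciling.

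Two further inferences go too far. A reader might calculate a cap for TAU alone: 26/30 = 86.7% with demographics counted, or 24/30 = 80.0% if AEP is removed too. The 80% rule is not set by arm, and Table 1 lists AEP as Form (A/B) without saying that TAU lacks a version. A reader might also infer that the form already reveals allocation to the masked researcher. A form given to everyone does not identify the arm by being handed out, and its route of completion is not stated.

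**Conclusion.** The point holds at moderate severity. The mismatch between HRQ and HAq-II and the baseline scheduling are in the text and need no assumption beyond treating the HAq-II row as the alliance measure. The effect on the 80% criterion is conditional:

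- Under the literal per-measure wording, the form falls short of 80% over its four scheduled visits unless participants rate therapists from outside the trial, including at baseline.
- Under the pooled reading, the criterion can be met, but the inapplicable forms raise the retention needed from about 74% to about 84%. A trial with 80% retention, which passes the protocol's 70% retention rule, could miss the completion threshold for that reason alone.

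The pooled result assumes equal retention in both arms, otherwise full completion, inapplicable forms scored as not completed, and no non-trial therapists. If two-thirds or more of TAU participants had another therapist to rate, the shortfall at 80% retention would disappear. The recruitment, retention and session-attendance criteria are unaffected.

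**What to change.** 1. Name one alliance instrument in both the text and Table 1.
2. Remove its baseline administration and schedule it for COPESS participants at follow-ups after therapy has started. Limiting it to COPESS but keeping baseline would not be enough under the per-measure reading: the ceiling would be 90/120 = 75%.
3. State that the 80% criterion counts only forms that apply to the participant and visit, and say whether it is judged per measure or pooled.
4. A form given only to COPESS participants would reveal the arm, so have it completed and returned by a route that bypasses the masked researcher. The existing safeguard, "Participants will be reminded to keep the researcher blind to their allocation arm of the study", would not cover this.

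The cost is an edit to Table 1, a few sentences of wording and a separate return route for one form. Participant burden falls by 150 scheduled forms.

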### EQ-5D

The EQ-5D-5L is a validated six-item questionnaire measuring quality of life across five health dimensions (mobility, usual activities, self-care, pain/discomfort and anxiety/depression). Five items are measured on a five-point scale considering health that day. The final question asks individuals to signpost their health today on a 100-point scale (with zero indicating the worst health imaginable and 100 indicating the best) [47].

### The Client Service Receipt Inventory (CSRI)

The Client Service Receipt Inventory (CSRI) [48] will be used to collect healthcare resource use. This includes information on use of other primary and secondary care services, use of social services, disability payments received, personal costs related to mental health (e.g. expenditure on over-the- counter medication, expenditure on prescriptions), time off work and unpaid activities.

### Statistical analysis

As a feasibility study, we will not be carrying out hypothesis testing to determine if the intervention is effective. Data analysis will follow an Intention-To-Treat (ITT) protocol and will help inform power calculations for a future definitive COPESS trial. Attrition and reasons for drop-out will be recorded where possible. Therapists will keep records of the number of COPESS sessions participants attend and the researcher will monitor and record the same information for the data collection sessions. For participants who withdraw from the study, the researcher will follow-up with either the therapists or participants to record the reason(s) for study withdrawal. We will assess rates and types of missing data, and proportion of dropouts at different stages/pathways through the trial. We will also assess whether any of the measures display floor and/or ceiling effects. Guidance will be sought from the PAG on how to manage and minimise missing data and attrition over the study period (see earlier section further details on the role of the PAG).

Summary statistics will be used as appropriate (e.g. mean/standard deviation; median/inter-quartile range; proportion/ 95% confidence interval; data range) to describe and compare data for all participants on continuous scores for repetition of self-harm, depressive symptoms, and urges to self-harm, overall and by group. The range and standard deviation of secondary outcome measures, along with estimated attrition rate and average number recruited per practice, will be help inform sample size calculations for a future full-scale trial.

### Health economic analysis

The feasibility study will be used to develop a framework for a subsequent cost effectiveness analysis to be undertaken alongside a future RCT. In particular, economic evaluation methods will be developed and tested regarding the collection of resource use, costs and outcome data. Health care resource utilisation and absences from work will be collected for each patient during the study follow-up period using the CSRI questionnaire. Data from the feasibility study will be used to inform adaptation of the CSRI prior to a definitive full trial. Generic health-related quality of life (HRQoL) data will be collected using the EQ-5D-5L instrument.

### Qualitative study

At the time of feasibility trial consent, all participants will be asked if they are willing to be contacted for possible participation in a one-to-one interview. In-depth interviews will be conducted with participants from both arms of the feasibility trial at 4–8 weeks post-randomisation. The project adopts a comprehensive safety protocol which guides the management of risk and responses to experiences of distress. This protocol was developed jointly by researchers, clinicians and individuals with lived experience of self-harm. An experienced mental health researcher will conduct the interviews and assessments. The researcher will receive regular supervision from an experienced qualitative researcher.

We also aim to include participants who did not attend all COPESS therapy sessions. A purposive sample of participants will be interviewed to capture maximum variation in views and experience of those participating in the study. Sampling parameters will include (1) sociodemographic variables, (2) type of self-harm (injury or poisoning) and (3) feasibility trial arm allocation. Participants will be selected from both arms of the feasibility trial to provide an insight into experiences of COPESS and TAU, and to allow for comparison of these experiences. The interviews will assess understanding of, and acceptability of the intervention received (content and contexts, setting, etc.), perceived benefits and mechanisms of action, challenges to engagement and contextual factors seen to affect the impact of intervention. For participants in the TAU arm, the researcher will ask about their experience of trial participation with a focus on feasibility, study procedures and issues that may affect attrition and feasibility of a larger trial. Additionally, the researcher will explore the patient’s experience of mental health pathways within the NHS to date and whether they were aware of the COPESS intervention. Interviews will be analysed in batches and sampling will continue until no new themes emerge—we expect this to be around 16–20 interviews.

GPs at participating recruitment sites will be invited to be interviewed about their experience of recruiting participants for this study. Therapists will be invited to be interviewed about their experience of being trained in the therapy and delivering the therapy. These interviews will help gain a detailed understanding of the perceived effectiveness and acceptability of the treatment, implementation challenges, and any barriers to its uptake in a community setting. Interviews will last approximately 60 min, will be audio-recorded and transcribed verbatim. All transcripts will be anonymised.

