### Sample size

A conventional power calculation is not necessary to achieve the stated aims of this feasibility study, as we will not be formally testing the effectiveness of the intervention. Instead, we aim to recruit 60 participants, following recommendations that this is sufficient to assess feasibility outcomes and estimate key parameters, such as the standard deviation of potential outcomes, with adequate precision in order to inform the sample size for a definitive full trial [38, 39]. For example, with *N* = 60, an attrition rate of up to 35% can be determined to within 12 absolute percentage points with 95% confidence. To avoid high attrition rates, we will keep participants engaged via text and/or telephone reminders.

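### The researcher who must stay masked is also named as the qualitative interviewer, so as written the assessor learns the arm of about 27–33% of participants before their 12-week assessment

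*Protocol article*

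**What the plan says.** The Design section states: "The study is a single-blind, randomised controlled feasibility trial with an embedded qualitative process evaluation". Randomisation and blinding accepts that participants cannot be blinded, so the masking that remains is that of the assessor. The principal investigator tells the participant and the GP the allocation, "keeping the researcher completing study assessments masked to treatment allocation". Participants are reminded not to reveal their arm to the researcher, and a tally of accidental unblinding is to be kept.

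Secondary outcomes measures places the follow-up assessments: "to be conducted at 4, 8 and 12 weeks post-randomisation". The SITBI, described there as an interview-based measure that captures repeated self-harm, is scheduled at all three.

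The Qualitative study section says: "In-depth interviews will be conducted with participants from both arms of the feasibility trial at 4–8 weeks post-randomisation". It then says: "An experienced mental health researcher will conduct the interviews and assessments". Trial arm is one of the sampling parameters. The section also aims to include people who missed some COPESS sessions, asks about the intervention received, and sets separate topics for the TAU arm. On the number, it says "we expect this to be around 16–20 interviews".

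Statistical analysis adds that, for withdrawals, "the researcher will follow-up with either the therapists or participants to record the reason(s) for study withdrawal".

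**The concern.** Assessor masking is the only blinding this trial can have. One section promises it. Another gives the assessments to the person who interviews participants about their treatment, and does so while assessments are still outstanding. One part of the plan asks participants to conceal their arm from the researcher; another has the researcher ask about it.

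An interview-based rating of repeated self-harm is open to influence from a rater who knows the arm. Repetition of self-harm is to be summarised by group, and the spread of the secondary outcomes is to inform the sample size of a full trial. The Aims section also makes the feasibility of the trial procedures a question in its own right, and assessor masking is one of those procedures. A tally limited to accidental unblinding would not count cases that arise from following the plan, so a full trial could inherit a count that is too low.

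**Working it through.** The protocol gives no figure for the extent of planned unblinding, so there is none to reproduce. The check is a comparison of timings and roles, with one simple proportion.

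**1. Who does what.** Qualitative study names one experienced researcher for both interviews and assessments. Randomisation and blinding requires the person completing assessments to be masked. No section assigns the two roles to different people, moves the interviews after week 12, or provides a different assessor for interviewed participants.

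**2. Does the interview reveal the arm?** Yes. Allocation is a sampling parameter, non-completion of COPESS is a target characteristic, and the questions differ by arm. The interview cannot be run as described by someone who does not know the arm.

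**3. Timing.** Let t be the interview week, with t from 4 to 8.

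| Assessment | Does the interview come first? |
|---|---|
| Week 12 | Always: the gap is 12 − 8 = 4 to 12 − 4 = 8 weeks |
| Week 8 | Only if the interview precedes that participant's 8-week visit |
| Week 4 | Not established: the window opens at week 4 |

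**4. How many.** Inputs: 16–20 interviews (Qualitative study) and the target sample (Sample size: "we aim to recruit 60 participants"). The 16–20 is taken to mean trial participants, because GP and therapist interviews are introduced only afterwards.

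- Share of those randomised: 16/60 = 26.7% to 20/60 = 33.3%.
- Share of those still assessed, if retention is exactly at the 70% criterion and every interviewee is retained: 0.70 × 60 = 42, so 16/42 = 38.1% to 20/42 = 47.6%. This is a what-if, not a forecast.
- Share of those randomised who are not interviewed: 66.7–73.3%.

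**5. Which outcomes are exposed.** The primary criteria are recruitment to target, at least 70% retention in both arms, more than 40% of the COPESS arm attending all sessions, and at least 80% of questionnaires completed. None is rated by the assessor. The BDI-II is described as self-report, and most other measures as questionnaires. The SITBI is the measure described as interview-based, so it carries the main exposure: at week 12 for every interviewee, and at week 8 for some.

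**The case against.** The strongest reply is that the sentence on interviews and assessments may be loose wording in a condensed article. The term assessments is not defined there, and the sentence follows remarks on managing risk and distress. Other sections show more than one research worker: the screening section mentions a research assistant and members of the team, and Safety monitoring mentions research assistants in the plural. Nothing says outright that the same individual interviews a participant and later assesses that participant. This stands as a reason for caution about what will happen in practice. It does not remove the contradiction, because the Qualitative study section describes no other assessments and the text as written joins the two roles.

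The second reply is that little depends on it: no test of effectiveness is planned, no primary criterion is assessor-rated, and no blinding-feasibility criterion is set. That is correct and limits the severity. No calculation shows that partial unmasking would materially change the outcome variances.

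A reader might draw three stronger conclusions that the document does not support.

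- *Masking is lost for the whole trial.* It is not: about two-thirds or more of participants are not interviewed.
- *Withdrawal follow-up adds materially.* Contact with therapists is one of two options. Participants are invited to follow-up unless they have withdrawn completely, so complete withdrawers have no later assessment to bias.
- *The interviews come too early to cover the therapy.* COPESS is four weekly sessions plus a follow-up session four weeks later. If therapy starts promptly, the four sessions end at about week 4, when the interview window opens. At most, the follow-up session is missed.

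**Conclusion.** The contradiction is real and should be fixed, though it does not threaten the trial's primary conclusions. Following the text as written unmasks the assessor for about 27–33% of participants (16–20 of 60) before their 12-week assessment, and for an unstated subset before the 8-week assessment. The consequence is mainly an unmasked SITBI rating in data summarised by group, together with an unblinding tally that omits unblinding built into the plan.

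This rests on three assumptions: that assessments in the Qualitative study section means the trial's outcome assessments; that the 16–20 interviews are all with trial participants; and that recruitment reaches 60. If separate staff were always intended, the text needs correcting rather than the conduct of the trial.

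**What to change.** Amend the Qualitative study section to do one of the following:

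- hold each participant's interview after that participant's 12-week assessment; or
- keep the 4–8 week window, but have the interview done by an existing team member who does not assess that participant.

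In either case, the principal investigator, who already knows allocation, should draw the arm-based interview sample and make any contact with therapists about withdrawals. In Randomisation and blinding, record planned unblinding separately from accidental unblinding.

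**Cost.** The first option needs no extra staff or visits. It lengthens recall: an interview moved from weeks 4–8 to just after week 12 is about 4–8 weeks later. It may also lose some interviewees to attrition, notably those who did not attend all sessions, whom the section wants to include. The second option avoids both losses but needs a clear division of work within the team.
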